#### ActiGraph wGT3X-BT

The ActiGraph wGT3X-BT (Pensacola, FL, USA) is a tri-axial research-grade accelerometer that will be used to measure physical activity objectively. ActiGraph devices have been used extensively as a reference (e.g., gold-standard) device to measure free-living physical activity objectively in adults [29]. Monitors will be initialized to collect raw acceleration data at 30 Hz using ActiLife software (version 6.13.3). Upon download, data will be re-integrated to 60-s epochs, and non-wear time will be defined as ≥ 90 continuous minutes of zero counts, with allowance for 2 min of acceleration that are preceded and followed by at least 30 min of continuous zeros [59]. Usable data will be defined as follows: (a) a log sheet with a valid start date is submitted, (b) a monitor is worn for at least 4 days (including one weekend day) with at least 10 h of valid wear time per day, and (c) no evidence of monitor error (e.g., activity counts > 20,000 or lengthy strings of repeated activity counts). Unusable data will be treated as missing data. Average minutes per day of MVPA will be calculated based on established cut points (e.g., > 1952 counts per minute) [60].

The cost of an ActiGraph wGT3X-BT is approximately 225 USA dollars. The ActiGraph wGT3X-BT can store data up to 43 days and sync wirelessly with the ActiLife mobile application; however, the wireless function will be disabled to maximize battery life. A participant will not be able to view any physical activity displays while wearing this device. The pairing of the ActiGraph wGT3X-BT with the Fitbit Zip is based on previous research where at least a moderately high correlation and a moderate level of agreement between measures of average minutes per day of MVPA produced by these two accelerometers has been observed [47, 48].

#### Acceptability

The acceptability of accelerometer-based assessment of physical activity will be assessed with a modified version of a questionnaire used in previous research [46, 61]. The 11-item acceptability questionnaire used in this study consists of a mix of both Likert-scale quantitative (6) and open-ended qualitative (5) items. The first item assesses relevant previous experience “Have you ever wore a physical activity monitor (e.g., Fitbit) to measure physical activity prior to enrolling in this study?”, ___ no, ___ yes. The next eight items are matched pairs where a quantitative item is paired with a qualitative item to assess a particular aspect of acceptability (i.e., instructions, acceptability of wearing the belt, remembering to wear the belt, integration into daily routine). For example, the second item is “the instructions included in the physical activity monitoring package were easy to follow”, 1 = strongly disagree, 2 = disagree, 3 = neutral, 4 = agree, 5 = strongly agree. Whereas the third item is “If you selected disagree or strongly disagree for the previous item, will you please tell us why the instructions were difficult to follow?”. The penultimate item is “Would you be willing to wear the belt again as a part of a new research study?”, 0 = no, 1 = maybe, 2 = yes. The final item is “What, if anything, would you suggest that we change about how the belt is to be worn in this research study?”

#### Feasibility

The feasibility of accelerometer-based assessment of physical activity within the FFW online intervention will be assessed with descriptive statistics, Pearson’s correlation coefficient, and Bland-Altman analyses. Descriptive statistics will include recruitment rate, eligibility rate, consent rate, participation rates, and retention rates. The mathematical definition for each of these rates will be provided in the “Data analysis” section of this manuscript.

#### Self-reported physical activity

Self-reported physical activity will be measured with the long form of the IPAQ [40, 41]. The long form of the IPAQ is intended for individuals from 15 to 69 years old and purports to measure physical activity in four domains—leisure time, domestic and gardening, work-related, and transport-related—according to the frequency and duration of the physical activity performed in each domain during the previous week. The physical activities measured are separated according to their intensity, which is defined as a distinction between walking, moderate physical activities, and vigorous physical activities. Moderate activities are those that cause a small increase in respiratory frequency and require moderate physical exertion, and vigorous activities cause more breathing than normal, with hard physical exertion [41]. Average minutes per day of MVPA will be calculated based on IPAQ data processing guidelines [62].

#### W1, W2, and W3 survey battery

Instruments designed to measure demographic information, anthropometric characteristics, self-efficacy, and well-being will be included in the survey battery. Data on proposed demographic covariates of well-being [63] and/or physical activity [9] will be collected in the W1 survey battery and will include participant gender, age, race, education-level, marital status, and annual income. Residential zip code data will be collected in the W1 survey battery as a proxy for a host of built environment factors that may be related to an individual’s level of physical activity [9]. Anthropometric data will be assessed in the W1 through the W3 survey battery by asking each participant their height and weight. Demographic, zip code, and anthropometric variables are collectively referred to as covariates from this point forward.

#### Self-efficacy to comply

Participants will be asked to respond to the following item in the W1 survey battery: *How confident are you in your current ability to get yourself to complete at least 30 Fun For Wellness post-introductory challenges within the next four weeks? Thoughtfully completing 30 post-introductory Fun For Wellness challenges may take approximately 4 h.* A five category rating scale structure, where 0 = no confidence, 1 = low confidence, 2 = moderate confidence, 3 = high confidence and 4 = complete confidence, will be implemented for this item, and in all self-efficacy scales from this point forward, based on previous research on effective self-efficacy rating scale structures [64]. Asking participants at the onset of an intervention to make a projection about their compliance with the subsequent intervention is consistent with previous research on compliance [65].

#### Well-being self-efficacy

Well-being self-efficacy has been defined as the extent to which a person believes that they have the ability to achieve a positive state of affairs in important areas of their life [38]. Well-being self-efficacy will be measured at W1 through W3 with the well-being self-efficacy scale (WBSE scale) consistent with both the 2015 FFW efficacy trial [36] and the 2018 FFW effectiveness trial [37]. The 21-item WBSE scale purports to measure seven dimensions of well-being self-efficacy: interpersonal, community, occupational, physical, psychological, economic, and overall. Each of the seven dimensions of well-being self-efficacy purported to be measured by the WBSE scale has a unique item stem that references three different time periods—past (i.e., 30 days ago), present (i.e., right now), and future (i.e., 30 days from now). Evidence for the validity and reliability of scores derived from responses to the original shorter (i.e., 7-item) version of the WBSE scale has been provided [38]. Evidence for the validity and reliability of scores derived from responses to the more recent 21-item version of the WBSE scale, however, is not yet available because the expanded version of the scale is being piloted in the 2018 FFW effectiveness trial.

#### Well-being actions self-efficacy

Well-being actions self-efficacy has been defined as the extent to which a person believes that they have the ability to take actions that may improve the state of affairs in important areas of their life [37]. Well-being actions self-efficacy will be measured at W1 through W3 with the well-being actions self-efficacy scale (WBASE scale) consistent with the 2018 FFW effectiveness trial [37]. The WBASE scale purports to measure six dimensions of well-being actions self-efficacy: interpersonal, community, occupational, physical, psychological, and economic. Each of the six dimensions of well-being actions self-efficacy purported to be measured by the WBASE scale has three items designed to measure it. Evidence for the validity and reliability of scores derived from responses to the WBASE scale is not yet available because the newly developed scale is being piloted in the 2018 FFW effectiveness trial.

#### Physical activity self-efficacy

Physical activity self-efficacy will be measured at W1 through W3 with the physical activity self-efficacy scale (PASE scale) consistent with the 2018 FFW effectiveness trial [37]. The PASE scale is a modified version of the exercise self-efficacy scale [66]. The PASE scale was tailored for the FFW context to assess the extent to which an individual believes that they have the ability to engage in a recommended amount of weekly physical activity for health. The PASE scale is concordant with the IPAQ scale. Specifically, the 48-item PASE scale measures weekly physical activity self-efficacy across four general domains of life: leisure time, domestic and gardening, work-related, and transport-related. Each of the four domains has two unique stems (e.g., how confident are you in your current ability to engage in leisure-related physical activity at a vigorous level of intensity) that reference six increasing time periods (e.g., for at least 10 or 15 or 30 or 45 or 60 or 75 min in the next week). Evidence for the validity and reliability of scores derived from responses to the PASE scale is not yet available because the modified scale is being piloted in the 2018 FFW effectiveness trial.

#### Self-efficacy to regulate physical activity

Self-efficacy to regulate physical activity will be measured at W1 through W3 with the self-efficacy to regulate physical activity scale (SERPA scale) consistent with the 2018 FFW effectiveness trial [37]. The 13-item SERPA scale is a modified version of the barriers self-efficacy scale [67]. The SERPA scale was tailored for the FFW context to assess the extent to which an individual believes that he or she has the ability to overcome possible barriers to engagement in a recommended amount of weekly physical activity for health. Evidence for the validity and reliability of scores derived from responses to the SERPA scale is not yet available because the modified scale is being piloted in the 2018 FFW effectiveness trial.

The reason for including both the SERPA scale and the PASE scale is that the latter scale focuses on an individual’s beliefs in his or her ability to accomplish levels of a task while the former scale focuses on an individual’s beliefs to overcome possible barriers to accomplishing a task that he or she already knows how to do. Self-efficacy theory [8] posits that a self-efficacy level construct (e.g., physical activity self-efficacy) may play a central role in the initiation of a behavior (e.g., engaging in a recommended amount of weekly physical activity) while a self-regulatory efficacy (e.g., self-efficacy to regulate physical activity) may play a central role in the maintenance of a behavior (e.g., engaging in a recommended amount of weekly physical activity over time). The importance of both a self-efficacy level construct and a self-regulatory efficacy construct has been demonstrated in exercise contexts [66, 67].

#### Subjective well-being

Subjective well-being has been defined as an individual’s satisfaction with the state of affairs in important areas of their life [68]. Subjective well-being will be measured at W1 through W3 with the 21-item I COPPE scale [68] consistent with both the 2015 FFW efficacy trial [36] and the 2018 FFW effectiveness trial [37]. The I COPPE scale is concordant with the WBSE scale. Specifically, the seven dimensions of subjective well-being purported to be measured by the I COPPE scale—interpersonal, community, occupational, physical, psychological, economic, and overall—match the seven dimensions of well-being self-efficacy that the WBSE scale was designed to measure. Each of the seven dimensions of subjective well-being purported to be measured by the I COPPE scale is measured with a unique item stem that references three different time periods: past, present, and future. Responses to each item follow an 11-category rating scale structure: from 0 (*worst your life can be*) to 10 (*best your life can be*). Evidence for the validity and reliability of scores derived from responses to the I COPPE scale has been provided [36, 68–70].

#### Well-being actions

The well-being actions construct has been defined as an individual’s actions that may improve the state of affairs in important areas of their life [39]. Well-being actions will be measured at W1 through W3 with the I COPPE actions scale [71] consistent with both the 2015 FFW efficacy trial [36] and the 2018 FFW effectiveness trial [37]. The 18-item I COPPE actions scale is concordant with the WBASE scale. Specifically, the six dimensions of well-being actions purported to be measured by the I COPPE actions scale—interpersonal, community, occupational, physical, psychological, and economic—match the six dimensions of well-being actions self-efficacy that the WBASE scale was designed to measure. Each of the six dimensions of well-being actions purported to be measured by the I COPPE actions scale has three items designed to measure it. Responses to each item follow a 7-category rating scale structure: from 0 (*never*) to 6 (*always*). Evidence for the validity and reliability of scores derived from responses to the original shorter (i.e., 12-item) version of the I COPPE actions scale has been provided [39, 71]. Evidence for the validity and reliability of scores derived from responses to the more recent 18-item version of the I COPPE actions scale, however, is not yet available because the expanded version of the scale is being piloted in the 2018 FFW effectiveness trial.

### Data analysis

Data analyses will include both quantitative and qualitative approaches. Quantitative analyses will be performed in M*plus* 8.0 under maximum-likelihood estimation with robust standard errors [72]. Missing data will be handled with the default approach under the assumption that data are missing at random [73]. When an estimate of a population parameter (e.g., mean difference) is sought, estimation of a 95% confidence interval (CI) will also be sought. When a qualitative approach is taken (e.g., responses to an open-ended acceptability item; feedback from the center staff), feedback will be summarized based on themes that emerge from the research team’s analysis of the feedback. The particular quantitative and/or qualitative methods that will be used to evaluate each specific aim will vary as a function of the focus of the specific aim.

A traffic light system will be used to evaluate results of specific indicators within each specific aim and with regard to the feasibility of a future definitive RCT [43]. Data observed below a lower threshold (i.e., red light) will indicate a potentially serious problem. Data observed above a lower threshold but below an upper threshold (i.e., yellow light) will indicate that caution is warranted. Data observed above an upper threshold (i.e., green light) will indicate support for the feasibility of a future definitive RCT. The particular threshold values that define the traffic light system will vary by the specific indicator within each specific aim (see Table 2).

**Table 2 Tab2:** Lower and upper bound threshold values that define the traffic light system by aim

Aim	Lower bound threshold	Upper bound threshold
Aim 1		
Acceptability	< 60%	≥ 80%
Recruitment rate	< 40%	≥ 60%
Eligibility rate	< 60%	≥ 80%
Consent rate	< 80%	≥ 90%
Participation rates	< 50%	≥ 70%
Retention rates	< 40%	≥ 60%
Aim 2		
Pearson’s correlation	< .60	≥ .70
Bland-Altman analyses	> 10% of observations beyond M ± 2SD	≤ 5% of observations beyond M ± 2SD
Aim 3		
Acceptability: Quantitative	< 75%	≥ 85%
Acceptability: Qualitative	At least one potentially serious problem	Absence of a potentially serious problem
Aim 4		
Intent to treat	< 0.00	≥ 0.20
Complier average causal effect	< 0.00	≥ 0.20
Indirect effects	Not available	Not available

#### Aim 1

Descriptive statistics will be used to determine if accelerometer-based assessment of physical activity *can* be used within the FFW intervention. Threshold values for the traffic light system for each of the specific indicators that will be used to evaluate aim 1 are based on inferences drawn from the results of previous research [22, 34, 46].

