### Randomization

Following completion of the W1 survey battery, participants will be randomly assigned to either the FFW group or the usual care (i.e., UC) group by the code programmed within the FFW website that is specified to achieve a 1:1 group (i.e., *n*_FFW_ = 15_,_
*n*_UC_ = 15) assignment.

Participants, center staff, and research staff will be blinded to participant group assignment.

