### Data collection

#### Study timeline

Three waves of data will be collected over a 13-week period (see Fig. 3), which is similar to both the 2015 FFW efficacy trial [36] and the 2018 FFW effectiveness trial [37]. Data collection at W1 will include the W1 survey battery and W1 physical activity monitoring. The W1 survey battery will be completed in week 1. The W1 physical activity monitoring will be completed in week 2. Participants will return physical activity monitoring items (to be detailed in the physical activity monitoring section) to the research staff in week 3. The intervention will be delivered in week 3 through week 6. Data collection at W2 will include the W2 survey battery and W2 physical activity monitoring. The W2 survey battery will be completed in week 7. The W2 physical activity monitoring will be completed in week 8. Participants will return physical activity monitoring items to the research staff in week 9. Data collection at W3 will include the W3 survey battery and W3 physical activity monitoring. The W3 survey battery will be completed in week 11. The W3 physical activity monitoring will be completed in week 12. Participants will return physical activity monitoring items to the research staff in week 13. The timeline for this study is similar to timelines used in other physical activity interventions in adults with obesity [6, 32, 33].

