#### W1, W2, and W3 physical activity monitoring

Instruments designed to measure physical activity and the acceptability and feasibility of accelerometer-based assessment of physical activity will be included in the PAMP. Research staff will prepare and send the PAMP to each participant via regular USA mail approximately 1 week before physical activity monitoring is scheduled to occur. A commercial-grade (Fitbit Zip) and a research-grade (Actigraph wGT3X-BT) accelerometer will be initialized and attached to an adjustable nylon belt to measure physical activity objectively. The order of the two monitors (i.e., which monitor is medial or lateral) will be randomized to account for small differences by wear location. The same two monitors will be provided to each participant at each time point to limit inter-monitor variability. Throughout the study duration, no app, firmware, or software updates will be allowed and one laptop computer will be used for all monitors, to ensure consistent clock times for data analysis. The primary measure of physical activity in this study will be the average minutes per day of MVPA based on both widely accepted recommendations for health-enhancing physical activity [3, 4] and the particular physical activity emphasis manifest in the FFW intervention [37].

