##### Acceptability: qualitative

Themes that emerge from responses to the five qualitative items designed to assess acceptability will be analyzed at wave *W*, where *W* = W1 or W2 or W3. Possible improvements will be considered with regard to the protocol for accelerometer-based assessment of free-living physical activity within the FFW online intervention among adults with obesity in the USA. Specifically, improvements will be considered with regard to instructions for wearing the belt, acceptability of wearing of the belt, remembering to wear the belt, integration of wearing the belt into the daily routine, and why some participants may be unwilling to wear the belt as a part of new research study. The lower bound threshold is the presence of at least one potentially serious problem with the accelerometer-based protocol that is unable to be addressed in a future study. The upper bound threshold is the absence of a potentially serious problem with the accelerometer-based protocol that is unable to be addressed in a future study.

#### Aim 4

Inferential statistical models under both an intent to treat (ITT) approach and a complier average causal effect (CACE) approach will be used to provide a preliminary effect size estimate for each direct effect depicted in the conceptual model (see Fig. 2) for the FFW online intervention (e.g., FFW → Physical Activity) at wave W, where W = W2 or W3. Using both an ITT approach and a CACE approach is consistent with data analyses from the 2015 FFW efficacy trial [36, 38, 39] and with the data analysis plan for the 2018 FFW effectiveness trial [37]. Covariates, the outcome at W1, and group assignment will be specified as predictors in both approaches. Threshold values for the traffic light system for the specific indicators that will be used to evaluate aim 4 are based on commonly used heuristics for Cohen’s *d* [76].

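### In the physical activity models, default maximum likelihood drops randomised participants who lack a W1 value, so the analysis called ITT omits some people with usable W2 or W3 data

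*Protocol article*

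**What the plan says.** All references are to the protocol article.

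- **Data analysis** names Mplus 8.0, maximum likelihood and robust standard errors, and then: "Missing data will be handled with the default approach under the assumption that data are missing at random". It mentions neither imputation nor a model for incomplete predictors.
- **Aim 4** specifies the models: "Covariates, the outcome at W1, and group assignment will be specified as predictors in both approaches". The two approaches are ITT and CACE.
- **ActiGraph wGT3X-BT** requires a log sheet with a valid start date, no monitor error, and that "a monitor is worn for at least 4 days (including one weekend day) with at least 10 h of valid wear time per day". It adds: "Unusable data will be treated as missing data".
- **W1, W2, and W3 physical activity monitoring** names the leading activity variable: "The primary measure of physical activity in this study will be the average minutes per day of MVPA". The IPAQ prompt goes out on the day after each 7-day wear interval.
- **Randomization**: "Following completion of the W1 survey battery, participants will be randomly assigned". **Study timeline** puts that survey in week 1, and then: "The W1 physical activity monitoring will be completed in week 2". Delivery of the intervention starts in week 3.
- **Participation rates** and **Retention rates** set the green thresholds at 70% usable per wave and 60% usable from W1 through a later wave. The red thresholds are below 50% and below 40%.

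**The concern.** Each of these choices is ordinary taken singly. Together they conflict with the ITT label for physical activity. The missing-at-random statement reads as if incomplete participants are kept, but default likelihood handling gives that protection to outcomes and not to predictors. W1 activity is measured after randomisation, so a participant can be randomised, fail the wear or log rule in week 2, and then supply good data at W2 and W3. Such a participant is in the trial and has the outcome, yet does not contribute to the estimate of the effect of assignment. Enrolment is capped at 30 by budget, so giving up collected outcomes is avoidable waste.

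**Working it through.** **Mechanism.** With W1 activity x, covariates z, group g and later activity y, the model described under Aim 4 maximises the product over participants of f(y | x, z, g).

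- If y is missing and x is observed, the case drops out of the product without harm under missing at random.
- If x is missing and y is observed, f(y | x, z, g) cannot be evaluated. The case can be kept only if x is given its own distribution, so that f(y, x | z, g) is maximised instead. That is an addition to the default, and the article does not state it.

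**Which models are exposed.**

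| Outcome | Source of W1 value | Timing against randomisation | Exposed? |
|---|---|---|---|
| Accelerometer MVPA | Week 2 wear, usable-data rule | After | Yes |
| IPAQ MVPA | Prompt after the wear week | After | Yes, through non-response |
| Self-efficacy, subjective well-being, well-being actions | W1 survey battery | Before | Not to the accelerometer rule; only to item or covariate non-response |

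**Counts for accelerometer MVPA at W2.** The inputs are 30 participants (Sample size) and the plan's own thresholds, taking the number consented as the number randomised. The article forecasts no usable-data rates, so the thresholds serve as the range.

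- Usable at W2 at the green level: 0.70 × 30 = 21.
- Usable at W1 and W2 at the green level: 0.60 × 30 = 18. Lost although W2 is usable: 21 − 18 = 3.
- Independent usability at 70% per wave: 0.70 × 0.70 × 30 = 14.7. Lost: 21 − 14.7 = 6.3, about 6.
- Limits when both waves are at 70%: overlap lies between 0.70 + 0.70 − 1 = 40% and 70%, so the loss lies between 21 − 12 = 9 and 21 − 21 = 0.
- At the red boundaries (50% per wave, 40% at both): 15 − 12 = 3 lost.

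**Precision.** Simulated trials had n = 30, true d = 0.2, no other covariates and missingness unrelated to arm. Two estimates of the group effect were compared: regression on cases with both waves, and joint maximum likelihood for W1 and W2 with equal W1 means across arms. The W1-W2 correlation is not in the article and is an assumption. At 0.6:

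| Pattern | SD, both-wave cases only | SD, joint model | Reduction | Variance ratio |
|---|---|---|---|---|
| 60% both, 10% W1 only, 10% W2 only | 0.400 | 0.380 | 1 − 0.380/0.400 = 5% | (0.400/0.380)² = 1.11 |
| Independent, 70% per wave | 0.449 | 0.388 | 1 − 0.388/0.449 = 14% | (0.449/0.388)² = 1.34 |

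Across assumed correlations from 0.8 down to 0.4, the reduction is roughly 3-10% in the first pattern and 9-17% in the second. No bias appeared under either approach when missingness was unrelated to arm.

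**The case against.** **The default is not described.** The article never says that cases with a missing predictor are excluded, and a separate analysis plan might bring W1 into the likelihood. This stands in part: exclusion follows from the named method and the stated predictor role, not from an explicit sentence. But the article does fix the estimator, the missing-data rule and the role of W1. Those commitments together produce the loss, so this is more than an omitted detail.

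**The effect is modest and Aim 4 is unpowered.** This stands. With true d = 0.2 and a normal approximation, the chance of a red light (estimate below 0.00) is Φ(−0.2/0.400) = 30.9% against Φ(−0.2/0.380) = 29.9%. In the independent pattern it is 32.8% against 30.3%. The chance of green is 50% either way. Independence gives 49% usable at both waves, below the 60% green level, and wear habits within a person are probably correlated. The smaller figures are therefore the more plausible ones.

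**Three stronger readings that the article does not support:**

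- *Every ITT model loses these participants.* Self-efficacy and well-being outcomes take their W1 values from a survey completed before randomisation.
- *The comparison is biased because W1 wear follows allocation.* Wear is in week 2, delivery starts in week 3, and participants and staff are to be blinded. Differential W1 usability is possible, but the article gives no mechanism for it.
- *Nine to 15 of the 30 are needlessly lost.* That is the number without usable W1 data at 70% and 50% (30 − 21 and 30 − 15). Some of them would also lack W2 or W3 data and add little under any method.

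**Conclusion.** The point holds for the physical activity models under Aim 4, both ITT and CACE. As written, they leave out randomised participants who have a usable later outcome but no W1 value. At the plan's green levels that is about 3 of the 21 with W2 accelerometer data, and about 6 under independence. The price is a standard error that joint modelling could lower by roughly 3-10% or 9-17% respectively, and an ITT label that the analysed set does not meet. It is worth correcting because the remedy is cheap, not because a decision is likely to turn on it.

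The conclusion assumes that the default is applied without modification and that W1 enters as an ordinary predictor. The counts use the plan's thresholds as if they were the rates achieved. The precision figures rest on assumed W1-W2 correlations of 0.4 to 0.8, normal data and no further covariates.

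**What to change.** For the physical activity models, replace the bare reference to the default with a statement that the W1 outcome is part of the likelihood. Either estimate its mean and variance within the model, or model W1 to W3 jointly with equal W1 means across arms. The equality constraint is reasonable because W1 wear is scheduled before delivery. Every randomised participant with at least one usable wave then stays in the analysis. Report the number analysed per arm for each model.

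Treat incomplete categorical covariates (race, marital status, zip code) by a method suited to their type, such as multiple imputation, and not by assuming normality.

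The cost is a sentence or two and a few lines of model code, plus an imputation step if categorical covariates are incomplete. The downside is a normality assumption for W1 MVPA, which may be skewed in this population. The robust standard errors already planned lessen that problem but do not remove it.
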